## Abstract

**Introduction:**

Migraine is a common clinical disorder, ranks as the second most disabling disease worldwide, and often manifests with unilateral onset. Contralateral acupuncture (CAT), as a classical acupuncture method, has been proven to be effective in the treatment of migraine without aura (MWoA). However, its neural mechanisms have not been investigated using multimodal magnetic resonance imaging (MRI).

**Methods and analysis:**

In this multimodal neuroimaging randomized trial, a total of 96 female MWoA participants and 30 female healthy controls (HCs) will be recruited. The 96 female MWoA participants will be randomized into three groups: Group A (CAT group), Group B [ipsilateral acupuncture (IAT) group], and Group C (sham CAT group) in a 1:1:1 allocation ratio. Each group will receive 30 min of treatment every other day, three times a week, for 8 weeks, followed by an 8-week follow-up period. The primary outcome is the intensity of the migraine attack. Data will be collected at baseline (week 0), at the end of the 8-week treatment period (weeks 1–8), and during the 8-week follow-up (weeks 9–16). Adverse events will be recorded. Multimodal MRI scans will be conducted at baseline and after 8-week treatment.

**Discussion:**

This study hypothesized that CAT may treat MWoA by restoring pathological alterations in brain neural activity, particularly by restoring cross-integrated functional connectivity with periaqueductal gray (PAG) as the core pathological brain region. The findings will provide scientific evidence for CAT in the treatment of MWoA.

**Ethics and dissemination:**

The Medical Ethics Committee of the Second Affiliated Hospital of Yunnan University of Chinese Medicine has given study approval (approval no. 2022-006). This trial has been registered with the Chinese Clinical Trials Registry (registration no. ChiCTR2300069456). Peer-reviewed papers will be used to publicize the trial’s findings.

**Clinical trial registration:**

https://clinicaltrials.gov/, identifier ChiCTR2300069456.

## Introduction

Migraine is a common clinical neuro-vascular disorder that can affect individuals of any age. It is primarily characterized by recurrent episodes of severe throbbing headaches, often accompanied the symptoms such as nausea, vomiting, photophobia, and phonophobia (Bes et al., 2018). Migraine without aura (MWoA) is the most prevalent type, accounting for approximately 80% of cases (Bes et al., 2018). Studies (May and Schulte, 2016; GBD 2016 Headache Collaborators, 2018) have reported a global migraine prevalence of about 14.4%, with an estimated 3% of episodic migraines progressing to chronic migraines each year. Migraine has been recognized by the World Health Organization as one of the major neurological disabling diseases that imposes a substantial social burden (GBD 2016 Disease and Injury Incidence and Prevalence Collaborators, 2017; Burch et al., 2019; Peters, 2019). It ranks second only to stroke in terms of disability-adjusted life years lost (GBD 2015 Disease and Injury Incidence and Prevalence Collaborators, 2016).

The analgesic effect of acupuncture, the most widely used complementary alternative medicine method for MWoA, has gained international recognition. MWoA is now included in the recommended spectrum of diseases treated with acupuncture (Millstine et al., 2017). Numerous international clinical studies have demonstrated the effectiveness of acupuncture in preventing the recurrence of MWoA, reducing the number of days of migraine attacks (Zhao et al., 2017), alleviating the severity of pain attacks (Li et al., 2009), and improving patients’ quality of life (Yang et al., 2011). Furthermore, comprehensive guidelines for acupuncture-based migraine treatment have been developed in China (Jiao et al., 2016), and the clinical efficacy of acupuncture for prophylactic treatment of MWoA has been confirmed with minimal side effects (Linde et al., 2016; Zhao et al., 2017).

With the widespread application of magnetic resonance imaging (MRI) in migraine research and acupuncture’s mechanism, multiple studies (Russo et al., 2012; Tessitore et al., 2013; Li K. et al., 2015) have shown that migraine attacks are associated with abnormalities in the resting-state brain’s functional network connectivity. These abnormalities in brain function in migraine patients result from the cumulative effects of repeated pain episodes over an extended period of time (Goadsby et al., 2017). Consequently, investigating the pathogenesis of migraine and the mechanisms of acupuncture intervention at the MRI level has become a current research focus. Several ongoing studies aim to elucidate the functional brain mechanisms of acupuncture for migraine (Cheng et al., 2022; Hong et al., 2022). Some studies have confirmed that specific brain regions affected by acupuncture for MWoA, when compared to sham acupuncture, include the precentral gyrus, the postcentral gyrus, the hippocampus, the posterior cingulate gyrus, and the prefrontal cortex (Li K. et al., 2015). In comparison to acupuncture at non-meridian and non-acupoints, elevated blood oxygen level-dependent (BOLD) signals were observed in the orbitofrontal cortex, bilateral medial ventral part of the head of the medulla oblongata, the trigeminal complex, bilateral anastomosing midbrain, and the precentral gyrus (Li et al., 2017). Conversely, decreases were observed in the precuneus, the middle frontal gyrus, the posterior cingulate cortex, and the postcentral gyrus (Zhao et al., 2014; Qin et al., 2019). Regulation of brain functional activity in the posterior central gyrus may be one of the mechanisms of acupuncture in the treatment of MWoA (Frot et al., 2013).

Contralateral acupuncture (CAT), a classical acupuncture therapy, is widely used in the treatment of unilateral pain disorders and has demonstrated superior clinical efficacy (Whan et al., 2012; Gao et al., 2013). Migraine, characterized by predominantly one-sided pain, is a well-suited candidate for CAT. Our previous studies also support that CAT is effective in both acute and chronic migraine (Li et al., 2021, 2022, 2023; Huang et al., 2023). However, research on the brain function mechanism of acupuncture for migraine has mainly focused on unilateral or bilateral acupoints, with limited exploration of CAT. Studies on central brain mechanisms have indicated that needling acupoints on the left and right sides can yield different responses in terms of central function. For instance, needling the Yanglingquan acupoint on the left and right sides in healthy subjects resulted in significant differences in the regulation of various brain regions (Yeo et al., 2016). When comparing CAT and IAT for frozen shoulder treatment, CAT at the “Tiaokou” acupoint led to more pronounced pain reduction and improved shoulder joint function, and functional brain imaging revealed significant differences in the degree centrality of various brain regions, such as the cerebellum, thalamus, and posterior central gyrus (Yan et al., 2020), as well as differences in regional homogeneity (Zhang et al., 2018). Therefore, it is essential to explore the central neurological mechanism of CAT in the context of migraine.

The periaqueductal gray (PAG), a central structure in pain processing, forms a ring-shaped region with midbrain parietal dense neuronal nuclei. As a central brain region for pain modulation, the PAG is a focal point in functional magnetic resonance studies of acupuncture analgesia (Kong et al., 2010; Solstrand Dahlberg et al., 2018). Recent studies (Ito et al., 2016; Chen et al., 2017; Yu et al., 2021) have revealed altered functional structures within the PAG in migraine patients, disrupting upstream and downstream pain regulatory systems. We propose that the central mechanism of CAT for migraine is closely related to the PAG’s role in information transmission. Given the effectiveness of CAT in MWoA treatment, we have chosen the PAG as a region of interest (ROI) to explore how CAT influences brain functional connectivity (FC) in MWoA patients.

Hence, we designed this multimodal brain imaging trial with two aims: (1) to re-evaluate the efficacy of CAT in the treatment of MWoA by comparing CAT with sham CAT and ipsilateral acupuncture (IAT); and (2) to investigate the neural mechanism of CAT in treatment of MWoA by examining differences in the modulatory effects of CAT on the migraine pathology network compared to sham CAT and IAT through the integration of multimodal MRI. The findings of the study may investigate that the analgesic message of CAT can be delivered through one or more analgesic pathways centered on the PAG, and could provide high-quality evidence for the functional brain mechanisms of CAT for MWoA, as well as help provide valuable scientific support for clinical decision-making in the choice of CAT or IAT in the clinical acupuncture treatment of MWoA.

## Intervention and assessment tools

The materials and equipment involved in this study include acupuncture needles that will be used during treatment and non-penetrating retractable blunt needles used in the control group, routinely sterilized 75% alcohol and cotton swabs, and the Park sham acupuncture device (PSD) for blinding. MRI data will be acquired using a resonance scanner with a 16-channel phased-array head coil (3.0T GE Discovery 750; Milwaukee, WI, USA). Specific operational use is described in the Interventions and MRI data sections in the Methods section below.

## Methods

### Study design

This randomized clinical trial was designed to evaluate the treatment effect and neurological mechanisms of CAT on MWoA. A total of 96 female MWoA participants and 30 female healthy controls (HCs) will be enrolled. The study will last 20 weeks including a 4-week screening phase (week −4 to week 0), an 8-week treatment period (weeks 1–8), and an 8-week follow-up period (weeks 9–16). The enrollment schedules, interventions, and assessments are summarized in Table 1. During the screening phase, participants will be assessed headache diaries. Clinical outcomes will be evaluated after treatment and during the follow-up. Multimodal MRI scans will be performed at baseline and after treatment. A study flowchart is presented in Figure 1.

**TABLE 1 T1:** Study schedule for data measurements.

	Study period					
	Enrolment	Allocation	Treatment phase		Follow-up	
Timepoint	−4 week	0 week	4 week	8 week	12 week	16 week
**Enrolment**						
Eligibility screen	×					
Informed consent	×					
Physical examination	×					
Randomization		×				
**Interventions**						
Group A (*n* = 32)			×	×	×	×
Group B (*n* = 32)			×	×	×	×
Group C (*n* = 32)			×	×	×	×
HCs group (*n* = 30)		×				
**Assessments**						
MRI parameters		×		×		
Headache diary	×	×	×	×	×	×
MSQ		×	×	×	×	×
MIDAS		×	×	×	×	×
HIT6		×	×	×	×	×
PSQI		×	×	×	×	×
SAS		×	×	×	×	×
SDS		×	×	×	×	×
Blinding/credibility test				×		
**Participants safety**						
AE			×	×	×	×
Laboratory test*		×		×		×

*The laboratory test includes complete blood count and differential count, absolute neutrophil count, aspartate aminotransferase, alanine aminotransferase, total bilirubin, blood urea nitrogen, creatinine, albumin, and coagulation test.

Group A, contralateral acupuncture (CAT) group; Group B, ipsilateral acupuncture (IAT) group; Group C, Sham CAT group; HCs, healthy controls; MRI, magnetic resonance imaging; VAS, visual analog scale; MSQ, Migraine-Specific Quality of Life Questionnaire; MIDAS, Migraine Disability Assessment; HIT6, Headache Impact Test-6; PSQI, Pittsburgh Sleep Quality Index; SAS, Self-Rating Anxiety Scale; SDS, Self-Rating Depression Scale; AE, adverse events.

**FIGURE 1 F1:**
[figure not shown]
Flowchart of the research procedure.

This trial will be reported in accordance with the Standard Protocol Items: Recommendations for Intervention Trials (SPIRIT) guidelines (Chan et al., 2013; Supplementary File 1) and the Standards for Reporting Interventions in Clinical Trials of Acupuncture principles (STRICTA) (MacPherson et al., 2010). The protocol was approved by the Medical Ethics Committee of the Second Affiliated Hospital of Yunnan University of Chinese Medicine (2022-006) (Supplementary File 2) and is registered with the Chinese Clinical Trial Registry (registration no. ChiCTR2300069456).

### Recruitment and informed consent

All female MWoA participants and HCs will be recruited from the Second Affiliated Hospital of Yunnan University of Chinese Medicine and Kunming communities. Recruitment will take place through advertising from May 2023 to December 2024. Neurologists will strictly adhere to the inclusion and exclusion criteria to determine the eligibility of patients for this study. To facilitate recruitment, advertisements will be designed for both online platforms (e.g., WeChat public accounts and websites) and offline channels.

All participants will receive an explanation of the purpose and nature of this study protocol and they will be provided with comprehensive information about the study, including its procedures, potential benefits, and risks. Prior to enrollment, they will voluntarily sign an informed consent form (Supplementary File 3). All participants will have the option to withdraw from the study at any time without incurring penalties or losing benefits, and they are not required to provide a reason for their withdrawal. Any reasons for withdrawal will be documented.

### Participants

#### Inclusion criteria for patients with MWoA

(i) Meeting the diagnostic criteria for MWoA in the International Classification of Headache Disorders (ICHD-3) (Bes et al., 2018); (ii) right handed, female, high school or above education, aged 18–45 years old; (iii) in the past 3 months, the headache attack was ≥2 times per month, and the headache days were <15 days per month; (iv) moderate headache attacks (3 < visual analog scale (VAS) score < 7) (Lee et al., 2016) in the last 4 weeks (baseline period); (v) history of migraine for more than 1 year and no history of dysmenorrhea; (vi) no acupuncture or pharmacological treatment within 1 month; (vii) no metallic implants in the body and no MRI contraindications; and (viii) not participating in any other trials during the study period and signing a written informed consent form.

#### Exclusion criteria for patients with MWoA

(i) Bilateral or alternating unilateral migraine, or the presence of other chronic pain conditions (e.g., dysmenorrhoea, chronic low back pain, etc.); (ii) other types of headaches or headaches with an unknown diagnosis; (iii) presence of severe organ or physical illnesses, or severe mental health conditions such as anxiety, depression, insomnia, and other mental disorders; (iv) pregnancy, breastfeeding, or planning to give birth within the last year; (v) definite organic brain lesions or significant asymmetry between the right and left sides of the skull; (vi) contraindications to MRI (e.g., metallic foreign bodies, vascular stents, pacemakers, dentures, claustrophobia, etc.); (vii) current analgesic use or psychotropic drug dependence; (viii) populations with possible differences in brain structure and function, e.g., smoking or alcohol addictions; and (ix) participation in a similar study within the last 3 months.

#### Inclusion criteria for HCs

(i) Right handed, female, high school education or above, aged 18–45 years; (ii) no history of prolonged dysmenorrhoea, no neurological or psychiatric disorders, and no family history of a genetic predisposition; (iii) absence of physical abnormalities (e.g., cold, fever, etc.) during the trial; (iv) no medication or alcohol consumption at least 2 days prior to enrollment, and no use of stimulants for at least 1 month; and (v) willingness to participate and the ability to sign the informed consent form.

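### Healthy controls are not explicitly held to the chronic-pain, dysmenorrhoea and acupuncture criteria applied to patients, although they are the reference for the baseline PAG and grey-matter comparisons

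*Protocol article*

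**What the plan says.** The article prints four numbered criteria lists, two for patients and two for HCs.

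**Patients.** Inclusion (v) requires "history of migraine for more than 1 year and no history of dysmenorrhea". Exclusion (i) removes women with "the presence of other chronic pain conditions (e.g., dysmenorrhoea, chronic low back pain, etc" and similar conditions. Inclusion (vi) requires "no acupuncture or pharmacological treatment within 1 month", and exclusion (vii) removes "current analgesic use or psychotropic drug dependence".

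**HCs.** Inclusion (ii) requires "no history of prolonged dysmenorrhoea, no neurological or psychiatric disorders, and no family history of a genetic predisposition". Inclusion (iv) requires "no medication or alcohol consumption at least 2 days prior to enrollment, and no use of stimulants for at least 1 month". Inclusion (iii) asks for no physical abnormality, with a cold and fever as examples. The HC exclusions cover serious vital-organ disease, disability, alcohol or drug abuse, MRI contraindications, pregnancy and breastfeeding, and groups whose brain structure or function may differ, with smoking and alcohol addiction as examples. None of these names chronic pain or acupuncture.

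**Use of the HCs.** Under Neuroimaging data analysis, the first imaging step compares baseline PAG connectivity between patients and HCs with a two-sample t-test, and the morphometry analysis follows a similar procedure. The Introduction presents the PAG as a central region for pain modulation in general, not as specific to migraine.

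**The concern.** The plan removes other pain from the patients so that what remains can be attributed to migraine, but does not explicitly remove it from the comparator. The seed region responds to pain of many kinds. A control with ordinary dysmenorrhoea or chronic back pain may therefore carry some of the same alteration, and the reference would move towards the patients.

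At stake is the baseline contrast that describes what is abnormal in migraine. The Abstract's hypothesis is that contralateral acupuncture restores pathological alterations centred on the PAG, so this contrast frames how the later findings are read. With only 30 HCs, a few affected women count. Recent acupuncture in an HC is a related gap, since acupuncture is the intervention whose effect on the PAG is being studied.

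**Working it through.** **Step 1: criteria side by side.**

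| Topic | Patients | HCs |
|---|---|---|
| Dysmenorrhoea | no history (inclusion v); also named in exclusion (i) | no history of prolonged dysmenorrhoea only (inclusion ii) |
| Other chronic pain | excluded, low back pain named (exclusion i) | not named |
| Acupuncture | none within 1 month (inclusion vi) | not named |
| Medication | none within 1 month (inclusion vi); no current analgesic use (exclusion vii) | none for at least 2 days before enrolment (inclusion iv) |
| Alcohol and stimulants, short term | no interval given | alcohol 2 days, stimulants 1 month (inclusion iv) |
| Addiction | smoking or alcohol addiction excluded (viii) | same wording (exclusion vi) |

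**Step 2: do the general HC clauses close the pain gap?** The clause on possible brain differences, HC exclusion (vi), appears in the same words as patient exclusion (viii). In the patient list it stands beside a separate, explicit chronic-pain exclusion, so it was not relied on there to cover pain. The physical-abnormality clause is illustrated by acute illness. Either could be applied to a woman with chronic pain, but neither tells the screener to do so.

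**Step 3: is the medication gap as wide as 1 month against 2 days?** Not in practice. The section on urgent medication allows patients acute NSAIDs throughout the study. Study design counts the 4-week screening phase as part of the study, and Secondary outcomes record emergency medication from week −4. MRI data requires at least 72 h without migraine before a scan. A patient may therefore have taken an NSAID some days before her baseline scan, which is not far from the HC rule. The HC interval runs to enrolment, not to the scan.

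**Step 4: illustration of dilution.** The documents give no power or effect size for this contrast, so there is no figure to reproduce. The inputs are 96 patients and 30 HCs (Sample size calculation). The assumptions are a true standardised difference d = 0.6 at one region, a two-sided 5% test without FWE correction, and a share q of HCs with the same alteration as patients. The small extra spread that a mixture adds is ignored.

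- Expected contrast: d × (1 − q).
- Noncentrality: d × (1 − q) × √(96 × 30 / 126) = d × (1 − q) × 4.781, with 124 degrees of freedom and critical value 1.979.

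| q | contrast | noncentrality | power |
|---|---|---|---|
| 0 | 0.60 | 2.87 | 81% |
| 10% | 0.54 | 2.58 | 73% |
| 20% | 0.48 | 2.29 | 62% |
| 30% | 0.42 | 2.01 | 51% |

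For q from 0 to 30%, power falls from 66% to 38% at d = 0.5 and from 97% to 76% at d = 0.8. With 90 patients (3 × 30 completers, since the connectivity analysis is restricted to completers), the d = 0.6 figures are 81%, 72%, 62% and 51%.

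**The case against.** Five points deserve weight.

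- **The open-ended clauses.** A reader might infer that a woman with chronic back pain meets every HC criterion. The documents do not support that. Both general clauses are illustrative lists, and the Introduction attributes brain abnormalities in migraine to the cumulative effect of repeated pain, so a screener could exclude her as having possible brain differences. What stands is that chronic pain is not named and the outcome depends on the screener.
- **The drug interval.** A reader might also infer a large washout imbalance, 1 month against 2 days. Step 3 shows that it is narrower in practice. A 1-month no-drug rule for HCs alone could make them stricter than patients and create a new imbalance. This objection stands in full.
- **Adjustment.** It is tempting to say that pain status is not recorded in HCs and so cannot be adjusted for. The article does not say this. It does not list the HC case-report-form items, and the additional MRI procedures are in a supplement that is not shown.
- **The arithmetic.** Neither d nor q comes from the documents, the planned test is FWE-corrected, and HCs with pain are assumed to resemble patients. The figures show sensitivity; they do not estimate bias.
- **Reach.** On this model the contrast shrinks, so it would not manufacture a migraine difference. A reader might extend the problem to the treatment results, but the time-by-treatment ANOVA uses patients only, and nothing restricts it to regions found in the HC contrast.

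What survives is the stated difference on dysmenorrhoea, and the absence of any named chronic-pain or acupuncture criterion for HCs. Article length does not explain this: all four lists are printed, and prolonged is wording chosen for HCs alone.

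**Conclusion.** The point holds in a limited form. HCs face a looser dysmenorrhoea rule than patients and no named chronic-pain or acupuncture rule, while serving as the reference for a pain-modulation region. The likely consequence is dilution of the non-randomised patient-versus-HC contrasts in PAG connectivity and grey-matter volume. Its size cannot be determined from the documents. The illustrated fall from 81% to between 73% and 51% rests on an assumed d of 0.6, an assumed 10–30% of affected HCs, patient-like connectivity in those women, and a single uncorrected test. The alcohol and stimulant intervals are stated for HCs only, with no known size or direction of effect. The comparisons among contralateral, ipsilateral and sham acupuncture, and the VAS primary outcome, are untouched. This is a cheap improvement to the imaging reference group, not a threat to the trial's main result.

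**What to change.** 1. In the HC criteria, delete the word prolonged, so that any history of dysmenorrhoea excludes as it does for patients, and add that there must be no chronic pain condition, with the patients' examples.
2. Add the patients' 1-month no-acupuncture criterion for HCs.
3. Reconcile the medication, alcohol and stimulant intervals between the two groups and count them back from the MRI scan. The reconciled rule must take account of the acute NSAIDs that the plan allows patients, so a 1-month no-drug rule should not be imposed on HCs alone. Where the groups must differ, state why.
4. For HCs already enrolled, ask about pain history and repeat the baseline contrasts without those affected, as a sensitivity analysis.

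The cost is a few lines of wording, a few screening questions and one additional analysis. The downside is somewhat more screening to find 30 HCs.
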